| Objective(s): | In general, we are interested in the differences between the heart rate variability before and after caffeine supplementation and if exercise performance is enhanced using this type of supplementation. Another objective is to see whether there are differences between abled-bodied and disabled subjects as subjects with spinal cord injury have an impairment of the autonomic nervous system. |
| Outcome(s): | Primary outcome parameters are differences in heart rate variability and power output in the exercise performance test between caffeine and placebo trial. Secondary outcome parameters are epinephrine and norepinephrine concentration before and after caffeine supplementation, heart rate, tidal volume, lactate concentration before and after the exercise testing, as well as rating of perceived exertion after the exercise performance test. |
| Study design: | Randomised, double-blind, placebo controlled trial (RCT); pilot study |
| Inclusion / Exclusion criteria: | Inclusion: healthy, non-smoker, minimal 3x45 min physical activity per week, tetraplegic (C5 to C7) or paraplegic (sub Th8), AIS A, termination of first rehabilitation and more than 6 months after trauma.  Exclusion: drugs or supplements which influence heart rate variability, diabetes |
| Measurements and procedures: | Heart rate variability (HRV) is measured using a Polar heart rate monitor. After a 10min rest, HRV is measured during a 5 min phase in supine position and afterwards during a 6 min time period in sitting position. These measurements are conducted before the ingestion of the supplement, before the exercise performance test and after the exercise performance test.  Epinephrine and norepinephrine concentrations are measured before supplementation and one hour after supplementation (venous blood withdrawal).  Resting tidal volume is measured during the measurements of HRV.  Power output during the 3 min exercise performance test is analysed.  Lactate concentration is measured before and after the exercise performance testing taking a capillary blood sample.  Blood pressure is measured immediately before every HRV measurement.  Rate of perceived exertion is measured after the warm up and after the exercise performance test. |
| Study Product / Intervention: | Caffeine: 6 mg/kg body mass dosage, supplement will be ingested 1 hour before the exercise performance test respectively 45 min before the HRV measurement. |

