## Primary Objective

**Primary objective for HRV:** First of all we try to find out if caffeine supplementation alters the HRV at rest. From previous literature it is clearly stated that caffeine activates sympathetic nerves through the distribution of epinephrine and norepinephrine [31]. As in the HRV we can differentiate between components reflecting sympathetic and parasympathetic nerve activation, HRV should alter after the intake of caffeine supplementation. In our tetraplegic subjects there is a lack in the sympathetic innervation. Therefore, it is possible, that HRV or more precisely the sympathetic component of the HRV does not alter after the intake of caffeine. The following questions arise: What is the difference between paraplegic and able-bodied subjects in HRV after caffeine supplementation? Are there any differences comparing paraplegic, able-bodied and tetraplegic subjects with each other? Or does caffeine even not influence HRV in these different population groups?

**Primary objective for exercise performance:** Our aim is to investigate if caffeine enhances exercise performance in a 3 min exercise test at the arm crank ergometer. As studies with able-bodied subjects already showed some performance enhancing effects our focus lays on the spinal cord injured populations. Due to physiological adaptations after the spinal cord injury gut motility is slowed down and ANS activity is impaired. Therefore, absorption and also action of caffeine may be altered or even retarded. That`s why we want to know, if caffeine shows the same ergogenic effects on exercise performance in the spinal cord injured population as it shows in able-bodied subjects.

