## Secondary Objectives

As secondary objectives we want to test if caffeine increases catecholamine concentrations in the bloodstream in all three population groups and if there are any differences between these three groups.

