# STUDY OUTCOMES

## Primary Outcome

**Heart rate variability:** HRV difference between the measurement before the ingestion of caffeine compared to the measurement one hour after the ingestion of caffeine. This primary outcome gives us some further information about the effect of caffeine on the HRV and shows the differences between our three population groups.

**Exercise performance test:** We want to compare the power output between the two tests (placebo vs. caffeine) to know whether caffeine shows some ergogenic effects in the spinal cord injured population groups concerning arm crank exercise performance. To date, only one study examined exercise performance tests with the spinal cord injured population groups using caffeine as a supplementation [17]. These findings would provide some further information about caffeine supplementation in wheelchair sports.

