## Planned Analyses

### Datasets to be analysed, analysis populations

Only data from subjects who have completed the whole study protocol will be used for analysis. For each group, a minimum of 10 data sets will be analysed.

Analyses will be performed separately for the three subject groups (i.e. tetraplegic, paraplegic, able-bodied). No direct comparison between the groups will be performed.

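### The analysis section rules out any comparison between groups, although the primary and secondary objectives ask whether the caffeine response differs between them

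*Protocol*

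**What the plan says.** **What the protocol asks**

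- Synopsis, Objective(s): "Another objective is to see whether there are differences between abled-bodied and disabled subjects". The German summary likewise announces HRV comparisons both within and between the groups.
- Section 4.2, HRV: "What is the difference between paraplegic and able-bodied subjects in HRV after caffeine supplementation", and then "Are there any differences comparing paraplegic, able-bodied and tetraplegic subjects with each other".
- Section 4.2, exercise performance: "if caffeine shows the same ergogenic effects on exercise performance in the spinal cord injured population as it shows in able-bodied subjects".
- Section 4.3, catecholamines: "if caffeine increases catecholamine concentrations in the bloodstream in all three population groups and if there are any differences between these three groups".
- Section 5.1, on the HRV outcome: it "shows the differences between our three population groups".
- Section 3.8 describes the able-bodied men as a control for the men with spinal cord injury.

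**What the protocol allows**

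- Section 11.4.1: "Analyses will be performed separately for the three subject groups (i.e. tetraplegic, paraplegic, able-bodied"), followed directly by "No direct comparison between the groups will be performed".
- Sections 11.1 and 11.4.2 contain only placebo-versus-caffeine hypotheses, tested by Wilcoxon signed-rank in each group separately.
- Section 11.4.3 adds further signed-rank tests and one Spearman correlation. None of these compares groups.

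**The concern.** Part of the primary objective and part of the secondary objective have no analysis that could answer them. This is not a detail left for a statistical analysis plan: a plan that followed Section 11.4.1 would be barred from supplying the comparison.

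The practical risk lies in the write-up. A report that must address the objectives, and holds only three separate p-values per outcome, is drawn towards treating significance in one group and non-significance in another as evidence that the groups differ. That pattern does not test a difference. With about 10 men per group it occurs often even when caffeine acts identically in all three.

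**Working it through.** **Inputs.** Section 6.2.1 gives significance level 0.05, power 0.8, difference 7.59, SD 10 W, sample size 9, and 10 per group after 10% drop-out. Section 11.1 makes the alternatives two-sided. Section 11.2 requires at least 10 data sets per group. The protocol does not say whether 10 W is the SD of a single measurement or of the paired differences.

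**Step 1: reproduce the protocol's figure.** For a paired two-sided comparison, n = ((1.96 + 0.842) × SD / 7.59)².

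- SD of differences 10 W: n = 13.6, so 14 by the normal formula and 16 by the exact t calculation. With n = 9 the power is 52%.
- SD of differences 10/√2 = 7.07 W: n = 6.8 by the normal formula and exactly 9 by the t calculation (power 80.5%). If 10 W is the per-trial SD, this corresponds to a within-subject correlation of 0.75, which the protocol does not state.
- The drop-out step is right: 9 / 0.9 = 10.

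Of the readings tried, only 7.07 W gives exactly 9. Both values are carried forward as a range.

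**Step 2: how often separate tests disagree when the groups do not differ.** Assume a true effect of 7.59 W in every group, normally distributed differences and n = 10. The exact two-sided signed-rank test rejects when the smaller rank sum is 8 or less (p = 0.049). Let π be its power, found by simulation. Then

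- a given pair of groups disagrees with probability 2π(1 − π);
- the three groups fail to agree with probability 1 − π³ − (1 − π)³.

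| SD of paired differences | π | Given pair disagrees | Three groups not unanimous |
| --- | --- | --- | --- |
| 7.07 W | 0.84 | 27% | 41% |
| 10 W | 0.55 | 49% | 74% |

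No true group difference exists in any of these cases.

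**Step 3: what a direct comparison could deliver.** Compare the individual caffeine-minus-placebo differences of two groups of 10. The approximate 95% half-width is t(0.975; 18 df) × SD × √(2/10), with t = 2.10.

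| SD of paired differences | Half-width | Power for a 7.59 W contrast (two-sided t) | Contrast detectable with 80% power |
| --- | --- | --- | --- |
| 7.07 W | 2.10 × 7.07 × 0.447 = 6.6 W | 62% | 9.4 W |
| 10 W | 2.10 × 10 × 0.447 = 9.4 W | 36% | 13.2 W |

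If all 36 men of Section 11.2 completed (36 / 3 = 12 per group), power would be 71% and 43%.

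These figures concern power output only. The protocol gives no effect size or SD for HRV or catecholamines, so no such calculation is possible for them.

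**The case against.** The strongest defence is that this is a pilot whose formal hypotheses are within-group. Section 11.1 names two primary hypotheses, both caffeine against placebo, and Section 11.4.2 tests them. In the synopsis the group question comes as an additional objective. With 10 per group, declining formal between-group tests is a defensible choice, and Step 3 shows that such tests would be weak. All of this stands, but it does not reconcile Section 11.4.1 with Sections 4.2, 4.3 and 5.1. Low power is a reason to label a contrast exploratory, not to prohibit estimating what an objective asks for.

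Three stronger readings are tempting, and the document does not support them.

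- A reader might infer that the trial cannot answer its question at all. The within-group questions remain answerable.
- A reader might infer that the able-bodied group serves no purpose without a comparison. Section 3.1 gives it an aim of its own: to verify the performance effect of caffeine in able-bodied people.
- A reader might infer that the authors intend to draw group conclusions from discordant p-values. No section says so. Section 11 plans medians, quartiles, 95% confidence intervals and ranges, so the groups can be described side by side.

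Nor can it be said that disagreement between tests would arise in most trials whatever the SD: at 7.07 W it is a minority outcome.

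**Conclusion.** The contradiction is explicit and should be resolved before the data are analysed. It is confined to the between-group questions, which stand in the primary and secondary objectives and have no permitted inferential analysis.

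For power output, reading group differences from separate tests would mislead often: under an identical effect, verdicts disagree in 41% to 74% of trials across three groups and in 27% to 49% for any given pair. This rests on a common true effect of 7.59 W, normal differences, 10 men per group, and an SD of paired differences between 7.07 and 10 W, which Section 6.2.1 leaves open. The size of the problem for HRV and catecholamines cannot be calculated from the document.

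**What to change.** **Preferred.** Replace the last sentence of Section 11.4.1 with wording to this effect:

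- The individual caffeine-minus-placebo differences will be compared across groups as an exploratory analysis. For HRV and catecholamines, the quantity compared is the difference between treatments in the pre-to-post change.
- The tetraplegic versus able-bodied and paraplegic versus able-bodied contrasts will be reported as estimates with 95% confidence intervals, for example by rank-sum methods with Hodges-Lehmann intervals.
- No group difference will be inferred from separate within-group p-values.

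**Alternative.** If the sponsor wants no comparison, remove the between-group questions from the synopsis, the German summary and Sections 4.2, 4.3 and 5.1.

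**Cost.** Either route is a change of protocol wording and needs no new data; the first adds a few lines of analysis code. Its price is imprecision: at 10 per group the contrasts in power output carry half-widths of about 6.6 to 9.4 W, against a planning effect of 7.59 W, so the exploratory label is essential.

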### Primary Analysis

For testing the first hypothesis

H_0_: m_1_ = m_2_ versus
H_1_: m_1_ ≠ m_2_
where m_1_ = performance (power output) under placebo
 m_2_ = performance (power output) under caffeine

the Wilcoxon signed-rank test will be used to compare the performance under placebo with that under caffeine for three subject groups separately.

For testing the second hypothesis

H_0_: m_1_ = m_2_ versus
H_1_: m_1_ ≠ m_2_where m_1_ = change in HRV from baseline to post-treatment under placebo treatment
 m_2_ = change in HRV from baseline to post-treatment under caffeine treatment

the Wilcoxon signed-rank test will be used to compare the performance under placebo with that under caffeine for three subject groups separately.

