| Control Intervention (if applicable): | Placebo (mannitol) |
| Number of Participants with Rationale: | 30 participants in total (10 per each group of able-bodied, tetraplegic and paraplegic subjects): this study is a pilot study thus no power analysis was performed. |
| Study Duration: | 20 months |
| Study Schedule: | 01. May 2014: start of data collection  31. December 2015: end of data collection |
| Investigator(s): | [name]  Sports Medicine, Swiss Paraplegic Centre, [name], [contact], [contact] |
| Study Centre(s): | Single-center study: Swiss Paraplegic Centre Nottwil |
| Statistical Considerations: | For analysing the differences pre and post ingestion of caffeine within a subject, a Wilcoxon test will be used.  The correlation between HRV and performance under caffeine treatment will be evaluated with the Spearman’s rank correlation coefficient. |
| GCP Statement: | This study will be conducted in compliance with the protocol, the current version of the Declaration of Helsinki, the ICH-GCP or ISO EN 14155 (as far as applicable) as well as all national legal and regulatory requirements. |

study summary in local language can be provided here (German)

Die Herzfrequenzvariabilität (HRV) beschreibt die Varianz der Zeitintervalle zwischen den einzelnen Herzschlägen. Sie ist ein Parameter zur Bestimmung der Funktion des Sympathikus und Parasympathikus des autonomen Nervensystems. Diese beiden Komponenten haben antagonistische Aufgaben bei der Regulation der viszeralen Funktion des Körpers. Während der Sympathikus eine eher anregende Wirkung hat, hemmt der Parasympathikus.

Aus der Analyse der HRV resultieren zwei Komponenten, welche den zwei Systemen zugeordnet werden können. Die low frequency (LF) repräsentiert den Sympathikus während die high frequency (HF) dem Parasympathikus zugeordnet wird.

Je mehr also zum Beispiel der Sympathikus aktiviert ist, desto grösser ist der Anteil des LF- im Vergleich zur HF-Komponente. Mit der Analyse der HRV lassen sich so Aussagen über die sympathische-parasympathische Balance machen.

Bei querschnittgelähmten Personen ist durch die Verletzung des Rückenmarks auch das autonome Nervensystem betroffen. Davon ist, aufgrund seiner Austritthöhe entlang der Wirbelsäule bis ca. zum 6. Brustwirbel, nur der sympathische Anteil betroffen. Der Parasympathikus dagegen tritt auf Hirnstamm-Höhe aus und ist so nicht direkt von der Unterbrechung der Rückenmarks betroffen.

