# Background and Rationale

## Background and Rationale

Heart rate variability (HRV) analysis is a possibility to examine the functioning of the autonomic nervous system (ANS). The ANS is divided into a sympathetic and parasympathetic branch which can stimulate or inhibit the heart trough the sinoatrial node. The HRV represents the length variance of the beat to beat intervals between the individual heart rates and allows to examine the power of the two branches. During the analysis of the HRV, the low frequency represents the sympathetic whereas the high frequency represents the parasympathetic part.

The sympathetic nerves leave the spinal cord at different levels whereas the parasympathetic nerves originate from the brain stem. Therefore a lesion of the spinal cord has an effect on the sympathetic part of the ANS. The higher the lesion the more the sympathetic part is affected.

The analysis of the HRV in spinal cord injured people shows partly different results than in able-bodied subjects. In a study the low frequency component is not shown in some high level injured people [20]. Other studies discovered the sympathetic part as well in high level injured people but with a reduced power [13, 20, 32].

Because of the fact that the sympathetic nervous system doesn’t leave the spinal cord over the whole length of the spine, in low level injured people the sympathetic nervous system is only affected to the 6^th^ thoracic vertebra. A lesion under this segment hasn’t a direct effect on the cardiac innervation of the ANS. Studies examining the HRV in low level injured people show the appearance of both components but with a reduced power compared to healthy reference persons.

Hence stimulants of the ANS have an effect on the two components of HRV. The impact of caffeine, which represents such a stimulant on the HRV, have been examined already in several studies with able-bodied people [18, 25, 29, 34]. There is a wide divergence in results and the effect of caffeine on HRV in able-bodied people is not yet resolved definitively [21]. Meanwhile, the impact of caffeine on the performance shows an improvement in the short time anaerobic zone.

The effect of a caffeine supplementation on HRV in spinal cord injured people has not yet been examined whereas the performance enhancing effect in this group of people could not yet be answered conclusively.

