# STATISTICAL METHODS

This study is a pilot-study with a small sample size. Therefore, normal distribution of the data cannot be assumed. Descriptive statistics, i.e. median, 25/75% quartiles, 95% confidence intervals and range, will be used. A p-value of < 0.05 will be considered significant, even though multiple hypotheses will be tested.

The treatment period (i.e. sequence of placebo and caffeine treatment) will not be included into the statistical analysis, because the wash-out period (48h) is considered more than long enough to prevent any carry-over effect. Furthermore, the period effect is considered to be negligible, because study participants will undergo a training session before the collection of data in order to avoid any learning effect.

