## Hypothesis

In order to investigate the effect of caffeine on the performance and the HRV, the two following primary hypotheses will be tested:

1. H_0_: m_1_ = m_2_ versus
   H_1_: m_1_ ≠ m_2_
   where m_1_ = performance (power output) under placebo
    m_2_ = performance (power output) under caffeine

   This hypothesis will be tested for the three subject groups (i.e. tetraplegic, paraplegic, able-bodied).
2. H_0_: m_1_ = m_2_ versus
   H_1_: m_1_ ≠ m_2_
   where m_1_ = change in HRV from baseline to post-treatment under placebo treatment
    m_2_ = change in HRV from baseline to post-treatment under caffeine treatment

   This hypothesis will be tested for the three subject groups (i.e. tetraplegic, paraplegic, able-bodied).

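### The primary HRV outcome is defined in some places as an uncontrolled before-after change under caffeine and in others as a placebo-controlled change, and no HRV component or posture is designated primary

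*Protocol*

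**What the plan says.** The protocol describes the primary HRV comparison in two ways.

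**Before versus after caffeine, no placebo term**
- Section 5.1, Primary Outcome: "HRV difference between the measurement before the ingestion of caffeine compared to the measurement one hour after the ingestion of caffeine".
- Synopsis, Statistical Considerations: "For analysing the differences pre and post ingestion of caffeine within a subject, a Wilcoxon test will be used".
- The synopsis objectives row and the German summary lean the same way.

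**Caffeine versus placebo**
- Synopsis, Outcomes: "Primary outcome parameters are differences in heart rate variability and power output in the exercise performance test between caffeine and placebo trial".
- Section 11.1, second hypothesis: m1 is the change from baseline under placebo and m2 is the "change in HRV from baseline to post-treatment under caffeine treatment". Section 11.4.2 repeats these definitions.

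Below those definitions, Section 11.4.2 gives the test for the HRV hypothesis as "the Wilcoxon signed-rank test will be used to compare the performance under placebo with that under caffeine for three subject groups separately". The same sentence serves the power-output hypothesis.

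On the variable itself, Section 3.1 explains that "the low frequency represents the sympathetic whereas the high frequency represents the parasympathetic part", and Section 9.2 records HRV both supine (5 min) and sitting (6 min). Neither the outcome section nor the hypotheses choose among these. On error control, Section 11 states: "A p-value of < 0.05 will be considered significant, even though multiple hypotheses will be tested".

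**The concern.** The two definitions answer different questions and can give opposite answers on the same data. Section 6.1 puts a venous blood draw, capsule intake, a 40-min break, a further 10-min rest and a second supine-to-sitting sequence between the two recordings. Any of these may move HRV without caffeine. A caffeine-only before-after test would credit that movement to caffeine. The placebo session exists to measure it.

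The unnamed variable adds a second freedom. With two components and two postures on hand, whoever analyses the data must decide which result is the primary one, and the protocol does not constrain that decision. Every test is then called significant at 0.05.

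**Working it through.** **1. What each definition estimates.** Let d be the mean change in HRV over the interval without caffeine, and t the added effect of caffeine.

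- Before-after under caffeine (5.1, synopsis statistics): estimates d + t.
- Change under placebo: estimates d.
- Difference of the two changes (11.1): (d + t) − d = t.

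If caffeine does nothing (t = 0), the first version still tests whether d = 0. It holds its error rate only if d is exactly zero. The second needs no such assumption. The protocol gives no value for d, so the size of the bias cannot be stated. Its mechanism does not depend on that size.

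**2. Number of primary tests that follow from the text.** Two primary hypotheses (power output, HRV), each tested in three groups (11.1): 2 × 3 = 6. This takes HRV as a single variable.

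**3. Chance of at least one false positive, each test at 0.05.** The protocol states no such figure, so there is none to reproduce.

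- Independent tests: 1 − 0.95^6 = 0.265.
- The groups are different people, so independence between groups is sound. Within a group the two tests may be correlated. If they coincide completely, there are in effect three tests: 1 − 0.95^3 = 0.143.
- At the other extreme, each group's two tests can add to at most 0.10, giving 1 − 0.90^3 = 0.271 over independent groups. Whatever the dependence, the total cannot exceed 6 × 0.05 = 0.30.
- With exactly 10 data sets per group (the minimum in 11.2), the exact two-sided signed-rank test has an attained size of 50/1024 = 0.0488. That barely changes the result: 1 − 0.9512^6 = 0.259.

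The range is therefore about 14% to 30%, with about 26% as the central figure.

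**4. What a Holm correction within each group would do.** The smaller of the two p-values must be at most 0.05/2 = 0.025. At n = 10 the exact two-sided levels near that limit are 20/1024 = 0.0195 and 28/1024 = 0.0273, so the working threshold is 0.0195. Each group is held to 5%, but across three groups 1 − 0.95^3 = 14.3% remains.

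The cost in power can be illustrated with the 7.59 W difference and SD of 10 W in Section 6.2.1, assuming that the SD is that of the within-subject difference. Simulated signed-rank power at n = 10 falls from about 55% at 0.05 to about 37% at the Holm first step.

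**The case against.** The strongest reply is that the operative section is already right. Sections 11.1 and 11.4.2 both define m1 and m2 as changes under placebo and caffeine, the synopsis outcomes row agrees, and Section 11.4.3 compares the secondary changes between treatments. On this view, 5.1 and the synopsis statistics line are loose summaries. Much of this stands: a reader might infer that the trial plans to discard the placebo session, and no section says so. But 5.1 is the section that defines the primary outcome, and the synopsis line is a test statement. No sentence in the protocol correctly states the test for the placebo-controlled HRV change.

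It is also tempting to say that the HRV hypothesis will be tested on the wrong variable. The sentence sits directly under m1 and m2 defined as HRV changes, so it is a copying slip and an editorial matter.

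On multiplicity, the protocol declares itself a pilot and openly declines to adjust. That is a disclosed choice, not an oversight. A reader might go further and count both components in both postures as primary. With power output that makes 5 × 3 = 15 tests and 1 − 0.95^15 = 54%. No section makes all four HRV measures primary, and measures from the same person and session are not independent, so that figure is not supported. Nor is any numerical false-positive rate for the before-after test, because the protocol gives no drift to base it on.

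A statistical analysis plan may hold the computational detail of HRV. Which HRV variable is primary belongs to the outcome definition, and the protocol leaves it open.

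**Conclusion.** The point holds in this form. The primary HRV outcome is defined inconsistently, and one of the two definitions is uncontrolled and confounds caffeine with time, rest and repeated measurement. This is wrong as written and should be corrected; it does not rest on any assumed drift. The absence of a designated component and posture is a second real gap.

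The wording of the HRV test sentence is a minor correction. Unadjusted testing is a disclosed choice whose consequence is not stated: about 26% for six independent tests at 0.05, and about 14% to 30% across possible dependence. That count assumes one HRV variable, which the protocol has yet to name.

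**What to change.** 1. Use the Section 11.1 definition throughout: within-subject change under caffeine versus change under placebo. Rewrite Section 5.1 and the synopsis statistics line to match.
2. In Section 11.4.2, make the second test sentence refer to the change in HRV instead of performance.
3. Name one primary HRV component and one posture; the other HRV measures become secondary. The choice should take into account that the protocol describes the low-frequency component as absent or reduced in high-level injury (German summary, 3.1) and some HRV components as undetectable in some spinal cord injured subjects (3.4). Missing or floor values could cause ties in the signed-rank test in the tetraplegic group.
4. Fix that choice before any data are analysed. Unblinding is too late a deadline: Sections 6.2.2 and 6.3 keep the envelope sealed until the analysis is finished, by which time the two-sided A-versus-B p-values are known.
5. On multiplicity, at the sponsor's choice, either state the six-test error rate and label the p-values exploratory, or adopt a correction. Holm within each group is one option, with the residual 14% across groups and the 0.0195 threshold at n = 10 stated.

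Items 1 to 4 are wording changes and need no new data. Item 5 costs nothing if the tests are labelled exploratory; a correction costs power in groups that are already small.
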